#### Secondary outcomes.

We will calculate the number and percentage of participants experiencing at least one adverse event, and the total number of adverse events reported. We will tabulate the distribution of adverse events by severity (mild, moderate, severe) for both the rectal swab and bulk faeces groups. Summarise AEs by expectedness (expected, unexpected) and relatedness (definitely, probably, possibly, unrelated) for each group. We will report the incidence rates of adverse events per 100 participant-days for each group, allowing for comparison over different follow-up periods. We will use chi-square tests or Fisher’s exact tests to compare the incidence rates of adverse events between the rectal swab and bulk faeces groups. We will use ordinal logistic regression to analyse the severity of adverse events, treating severity as an ordinal outcome. We will include group (rectal swab vs. bulk faeces) as the main predictor and adjust for potential confounders (e.g., age, gender, mode of testing, and location of testing).

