### Risks and harm

Risks associated with the rectal swab sample collection process include discomfort or pain, and in rare cases, infection. In some cases, participants may experience minimal bleeding. There is a low to medium risk of these events occurring if sample collection is conducted properly. These risks are outlined in the patient information and consent form, ensuring that participants are fully informed prior to their involvement. To mitigate these risks, strict adherence to hygiene and sterile techniques is emphasized during both self-collection and clinician-guided collection.

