#### Follow-up.

Each person will receive a follow-up phone call after the test has been completed. The participant will be asked structured questions regarding the testing procedure:

“Which sample did you collect first?” (bulk/swab). This will help to validate the timing of sample collection, ensuring that samples that were collected close together (e.g., the participant records the same collection time for the swab and container) in time can be ordered.“Did you experience an adverse event during or after collecting the swab sample? (yes/no). If so, what was the nature of the event?” (qualitative). The adverse event will then be classified according to classification definitions described in ‘adverse event reporting and harms’.“Which test did you prefer?” (bulk/swab). “Why?” (qualitative)

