### Timeline

Participant recruitment is expected to commence in early 2025. Recruitment and data collection are expected to be completed within two years. Results are expected shortly after, placing the trial completion date in late 2027 or early 2028. It is expected that an average of 3–6 swabs will be obtained per week across collection sites. Some situations, such as outbreaks or mass gathering events, will allow for greater numbers of swabs to be collected in a small timeframe. After participants return the test samples, they will receive a follow-up phone call. Results of the bulk faeces test will be returned to the patient by the clinician that requested the test.

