#### Minimum data requirements.

At a minimum, data collected for each participant should include:

Identifiers (name, address, date of birth, contact details, comorbidities)Recruitment details (date of recruitment, date of consent, proof of consent, date that test packs were posted, symptomatology, duration of symptoms, presence of blood in faeces (if applicable))Sample collection details (where samples were collected (e.g., at home), who collected the sample (e.g., self-collect), date and time each sample was collected, date samples were submitted to pathology lab)Bulk faeces and rectal swab test results (date that lab testing was conducted for each sample, presence of visible faeces for the rectal swab only, positive/negative detection results for each sample)Follow-up information (date of follow-up attempts, which sample was collected first as reported by the participant, rough estimate of time difference between samples collected, adverse event details, preferred sample method)

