SeverityMild: Adverse events that are easily tolerated and do not interfere with daily activities. These could include minor discomfort or irritation at the site of the rectal swab.Moderate: Events that cause some interference with daily activities but are not dangerous. Examples may include moderate pain, cramping, or a temporary increase in bowel movement frequency.Severe: Events that significantly interfere with daily activities or pose a risk to health. Severe adverse events might involve intense pain, bleeding, or infection requiring medical intervention.ExpectednessExpected Adverse Events: These are events that are known to occur based on previous studies or the nature of the procedures. For rectal swabs, this could include expected mild discomfort or minor bleeding.Unexpected Adverse Events: Events that are not anticipated based on prior knowledge. Unexpected events could be severe allergic reactions, systemic infections, or unusual gastrointestinal symptoms.Relatedness to ProcedureDefinitely Related: There is a clear, direct link between the adverse event and the rectal swab procedure. An example is rectal bleeding immediately following the swab.Probably Related: There is a reasonable likelihood that the event is related to the procedure, but other factors could be involved. For instance, discomfort that occurs after the procedure and subsides soon afterward.Possibly Related: The event could be related to the procedure but could also be attributed to other causes. This might include abdominal pain occurring days after the procedure.Unrelated: The event has no apparent connection to the procedure. An example is an adverse event like a headache, which is likely due to other factors.4. Type of Adverse EventLocal Adverse Events: These are events occurring at the site of the rectal swab. They might include irritation, redness, or bleeding.Systemic Adverse Events: Events affecting the body beyond the local site, such as fever, nausea, or generalised infection.Procedure-Related Adverse Events: Specific to the process of specimen collection, like discomfort during the swab insertion or difficulties with the bulk faeces collection method.Non-Procedure-Related Adverse Events: Unrelated to the procedure itself, such as a common cold or unrelated illness occurring during the trial period.

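### For a one-off swab, adverse events per 100 participant-days mainly reflect when the follow-up call is made; the proportion already planned, over one common window, should be the incidence measure

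*Protocol article*

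**What the plan says.** The sentence at issue is under Statistical methods, Secondary outcomes: "We will report the incidence rates of adverse events per 100 participant-days for each group, allowing for comparison over different follow-up periods". The same paragraph first plans the count and percentage of participants with one or more events. It then plans to compare incidence between swab and bulk faeces by chi-square or Fisher's exact test.

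Events are collected by telephone. Under Follow-up: "Each person will receive a follow-up phone call after the test has been completed". Under Timeline: "After participants return the test samples, they will receive a follow-up phone call". The question put to the participant is "Did you experience an adverse event during or after collecting the swab sample", with no recall period attached. The text shown states no day, minimum or maximum for the call. Minimum data requirements lists "date of follow-up attempts, which sample was collected first as reported by the participant" and adverse event details, so the time to the call can be computed, but an onset date is not named as an item.

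On when events occur, Risks and harm says: "Risks associated with the rectal swab sample collection process include discomfort or pain, and in rare cases, infection". It gives no onset time. Adverse event reporting gives bleeding straight after the swab and short-lived discomfort as examples of related events. As an example of a possibly related one it gives abdominal pain: "This might include abdominal pain occurring days after the procedure".

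**The concern.** Dividing by participant-days corrects for unequal follow-up only if events accrue in proportion to time. The swab is inserted once and rotated for 10 to 15 seconds. Its risk is essentially per swab, concentrated at or shortly after collection. Each further day before the call then adds to the denominator and almost nothing to the numerator.

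The protocol's stated reason for the rate is that follow-up periods may differ. For this exposure the rate does the opposite of what is claimed: identical safety yields different figures according to when the call is made. A reader of the results could take a low rate as reassurance, or a high one as a warning, when either reflects telephone scheduling.

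A second, smaller issue is that a call made soon after collection could miss events that start later. Without a stated window, even the simple percentage has no defined period.

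**Working it through.** The protocol states no adverse-event rate and, in the text shown, no follow-up length, so there is no figure to reproduce. All event frequencies, onset times and call days below are assumptions chosen to show how the measure behaves.

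**1. How the rate behaves.** Let N be participants and t the days from collection to the call.
- Constant hazard h per day: events = N·h·t, so rate = 100·N·h·t/(N·t) = 100·h. It does not depend on t, and the protocol's reasoning would hold.
- Risk p at collection only: events = N·p, so rate = 100·N·p/(N·t) = 100·p/t. It is inversely proportional to t.

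**2. Illustration with immediate events only** (assumed 10 events in 300 participants, one per person):

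| Call day | Participant-days | Rate per 100 participant-days | Proportion |
|---|---|---|---|
| 1 | 300 | 100×10/300 = 3.33 | 3.3% |
| 7 | 2,100 | 100×10/2,100 = 0.476 | 3.3% |
| 14 | 4,200 | 100×10/4,200 = 0.238 | 3.3% |

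The rate varies 7-fold between days 1 and 7, and 14-fold between days 1 and 14, with safety unchanged.

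**3. Sensitivity to the event frequency.** With 5% immediate events the rate is 5.00, 0.71, 0.36 and 0.17 on days 1, 7, 14 and 30. With 2% it runs from 2.00 to 0.07 over days 1 to 30, and with 10% from 10.0 to 0.33. The dependence on t is the same in each case.

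**4. Adding some later events.** Assume 5% immediate plus 1% delayed, with exponential onset and a median of 4 days. Cumulative proportion = 0.05 + 0.01×(1 − 0.5^(t/4)); rate = 100 × that proportion / t.

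| Call day | Proportion | Rate per 100 participant-days |
|---|---|---|
| 1 | 5.2% | 5.16 |
| 7 | 5.7% | 0.81 |
| 14 | 5.9% | 0.42 |
| 30 | 6.0% | 0.20 |

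From day 1 to day 30 the proportion rises by less than one percentage point, while the rate falls about 26-fold (5.16/0.20).

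**5. What an early call could miss.** Share of delayed events already present at the call = 1 − 0.5^(t/median onset). For assumed medians of 3, 5 and 7 days:
- day 1: 21%, 13%, 9%
- day 7: 80%, 62%, 50%
- day 14: 96%, 86%, 75%

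**6. Effect on the swab-to-faeces comparison.** Methods describes a single group giving paired samples, so both so-called groups are the same people with the same call. Participant-days cancel from the ratio, which is unaffected by t.

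**7. Match with the planned test.** Chi-square and Fisher's exact tests take counts with and without an event. Participant-days do not enter, so these tests fit the proportion and not the rate they are said to compare.

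**The case against.** The strongest reply is that most of the remedy is already in the plan. The count and percentage with at least one event come first in the same paragraph, and the Primary outcomes section promises 95% confidence intervals for all estimates. That stands: the main safety description barely depends on call timing, and only the additional rate is badly chosen.

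It is also fair to say that the call day may be fixed elsewhere. Fig 1, the schedule of assessments, is not shown, and the article condenses a fuller protocol. So the documents do not establish that no interval exists. The objection to the rate survives either way. If one window applies to everybody, dividing by days serves no purpose; if follow-up differs, as the quoted sentence expects, dividing by days misleads.

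Several stronger readings are tempting but unsupported:
- **Delayed infection.** A reader might infer that the protocol itself identifies infection as a late event that the call will miss. It names infection as a rare risk with no onset time; the event it places days later is abdominal pain.
- **Lost events.** A reader might infer that anything starting after the call is never recorded. Packs carry contact details and, per the Discussion, the coordinator stays available, so spontaneous reports are possible.
- **Artefacts by site or collection mode.** No person-day comparison by either is planned. Mode and location of testing enter only as covariates in the ordinal model for severity, which uses no person-time.
- **Stopping for safety.** Decision rules refers to the incidence of severe events but does not tie it to participant-days.

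**Conclusion.** The point holds for the rate. Adverse events per 100 participant-days do not make different follow-up periods comparable for a one-off procedure whose named events mostly cluster at collection. In the illustration the absolute rate shifts 7- to 14-fold between a day-1 call and calls on day 7 or 14, with no change in safety. This rests on events being mostly immediate, which the protocol's own examples suggest, and on assumed frequencies and call days. The swab-to-faeces ratio, the planned tests and the accuracy outcomes are not affected.

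The related point about the window is conditional: the text shown gives no interval, and an early call could miss later symptoms, but Fig 1 may settle the timing. Because this concerns a secondary descriptive safety measure that sits beside a sound one, the severity is minor.

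**What to change.** In Statistical methods, Secondary outcomes, delete the rate per 100 participant-days. Name as the incidence measure the proportion of participants (one swab each) with at least one adverse event, with an exact 95% confidence interval. The chi-square or Fisher wording should then refer to proportions.

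In Follow-up and Timeline, state one ascertainment window, measured from swab collection and common to all participants, or point to Fig 1 if it already gives one. The call should come no earlier than the end of that window and ask about everything since collection. The trial team should choose a length that covers the later symptoms their own Adverse event reporting section anticipates. Recording the onset date among the adverse event details would let events be assigned to the window when a call runs late.

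The cost is a change of wording and the scheduling of a call that is already planned; no extra contact is needed. There is a real downside. The call also establishes which sample came first when the recorded collection times coincide, so label times cannot fully replace it. A later call slightly weakens recall of that order, and of mild discomfort.

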#### Missing data.

To minimise occurrences of missing data, the data collection tool will be designed in a clear and easy-to-operate format. Any members of the research team who may be responsible for data collection and data input will be familiarised with data collection/storage tools and processes, which will ultimately reduce occurrences of missing data due to an avoidable error. Minimum data requirements are defined within the data collection platform to ensure instances of missing data are easily identifiable and can be followed up promptly (e.g., missing symptomatology details).

Data relevant to consent, participant identifiers and dual samples must be reported at the bare minimum. We will require each site to monitor and report missing data every 6 months. If a participant withdraws from the study after providing consent, the reason for withdrawal will be recorded and taken into account in data analysis and interpretation stages. Non-critical missing data will be managed via sensitivity analyses, and if amenable, multiple imputation will be used. In the event that a participant does not return the swab (critical data), that participant will be contacted to check if they wish to withdraw from the study. If the individual wishes to remain part of the study, they will be supported to provide the additional sample (e.g., required sample kit will be provided again if necessary). Participants will be encouraged to supply the bulk faeces sample at a minimum to complete routine clinical or public health care. If the participant withdraws from the study, or is unable to be contacted, the participant’s data will be omitted.

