## Abstract

Obtaining a stool specimen for diagnostic testing of enteric conditions (e.g., gastroenteritis) can be a challenging and unpleasant experience. A person is required to obtain a sample pot from a healthcare location, return home and wait until they have a bowel motion, and then deal with the challenges of returning the sample to the clinic or pathology centre. This trial aims to identify whether the simpler approach of obtaining a rectal swab is effective for diagnosing enteric conditions. Recruitment will take place in a variety of settings, including suspected norovirus clusters, Hepatitis A clusters, in both hospital, and community settings. We will compare paired stool and rectal swab sample polymerase chain reaction (PCR) testing to determine whether rectal swabs are a reliable proxy for faecal sampling. Persons who would normally be provided with a faecal specimen container, will also be provided with a rectal swab for self-collection or clinician-collection (within 24 hours of the bulk faeces collection). We will assess the sensitivity, specificity, positive predictive value, negative predictive value using standard confusion matrix. The gold standard reference will be considered the bulk faeces PCR tests. We hypothesise that rectal swab PCR testing will be equally as effective as bulk faeces PCR testing. If successful, rectal swab PCR testing could be implemented as routine practice with several key benefits. Firstly, it would improve the patient experience by conveniently enabling stool collection at the point of care, which is rarely possible currently. Secondly, it would reduce healthcare costs, and streamline collection processes by eliminating the need for persons to return to a clinic to deliver specimen. Thirdly, the ease of testing will likely increase testing rates and compliance, leading to better diagnoses and more accurate clinical care. The protocol described has the potential to revolutionise daily clinical practice.

**Trial registration**: Australian New Zealand Clinical Trials Registry (ANZCTR): ACTRN12624000095561.

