### Outcomes

Primary Outcomes: Assess sensitivity, specificity, positive and negative predictive value, positive and negative agreement, accuracy, and receiver operating curves (at various CT value cutoffs), to determine the efficacy the new rectal swab approach.

Secondary outcomes: Acceptability of the rectal swabs in comparison to the gold standard of bulk faeces testing. This will be measured by asking participants which sampling method they preferred, and collecting information from participants in relation to any adverse events that may have occurred.

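### The rule for unreturned swabs permits pairs outside the 24-hour window, and swab preference is asked only of people who returned samples

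*Protocol article*

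**What the plan says.** **Pairing window.** The Abstract says the swab is collected "within 24 hours of the bulk faeces collection". The Methods do not repeat the limit. Collection process gives only a preferred order (swab first), and Minimum data requirements asks for the date and time of each sample.

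**Unreturned swab.** Under Missing data, a participant whose swab does not arrive is contacted. If they wish to stay in, "they will be supported to provide the additional sample (e.g., required sample kit will be provided again if necessary"). The same paragraph adds: "Participants will be encouraged to supply the bulk faeces sample at a minimum to complete routine clinical or public health care".

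**Remaining non-returners.** "If the participant withdraws from the study, or is unable to be contacted, the participant’s data will be omitted". Earlier in the section, for those who withdraw after consenting, "the reason for withdrawal will be recorded and taken into account in data analysis and interpretation stages". The Consent section describes not sending the swab as one way to decline or withdraw.

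**Acceptability.** This is the secondary outcome. "This will be measured by asking participants which sampling method they preferred", together with adverse event information. On timing, Follow-up says: "Each person will receive a follow-up phone call after the test has been completed". Timeline places that call after the samples have been returned.

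**Analysis.** Primary outcomes, under Statistical methods, scores swabs against bulk faeces PCR in 2x2 tables and gives no criterion for the interval between the two samples.

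**The concern.** The design treats each pair as two views of the same patient at nearly the same moment. The recovery rule can break that. A swab noticed as missing after the bulk sample has come in must be chased, a kit re-sent by post, and a new swab taken. That can hardly happen within 24 hours of the bulk collection. If the patient has cleared the organism by then, a negative swab against a positive bulk result counts as a false negative of the method when it reflects a change in the patient.

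The second issue concerns who is asked. Someone who finds the swab unacceptable and does not send it may never reach the preference question, and is then omitted if they withdraw or cannot be contacted. Acceptability would be estimated among people who have already accepted the swab.

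**Working it through.** **1. The plan's own figures.** For sensitivity Se, half-width d and proportion positive P, n = 1.96² × Se(1 − Se) / (d² × P). The text does not state d, so it is assumed here.

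- Se = 0.95, d = 0.10: 3.8415 × 0.0475 / 0.01 = 18.25 positives. Dividing by 0.30 gives 60.8, so 61; dividing by 0.20 gives 91.2, so 92.
- Se = 0.95, d = 0.05: 3.8415 × 0.0475 / 0.0025 = 72.99, so 73 positives.

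The stated 61, 92 and 73 all reproduce, so no stated figure is at fault. The 73 positives per pathogen subgroup correspond to a precision of about 5 points.

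**2. What the rule permits.**

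- The trigger is a missing swab, and the remedy refers to one further sample.
- The bulk sample is encouraged regardless, and Consent foresees one or both samples coming back. A bulk sample in hand with no swab is therefore an expected case.
- No sentence sets a deadline, calls for a new bulk sample, or says how an out-of-window pair is analysed.

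**3. Effect of late pairs on sensitivity.** Let f be the share of reference-positive pairs with a late swab, and r the chance that a late swab still detects the organism, relative to a timely one. Then observed Se = 0.95 × [(1 − f) + f × r]. The documents give neither f nor r, so both are assumed.

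| f | r = 1 | r = 0.8 | r = 0.5 | r = 0.2 |
|---|---|---|---|---|
| 5% | 0.950 | 0.941 | 0.926 | 0.912 |
| 10% | 0.950 | 0.931 | 0.903 | 0.874 |
| 20% | 0.950 | 0.912 | 0.855 | 0.798 |

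The share of late pairs that costs 5 points is f = 0.05 / [0.95 × (1 − r)]: 26% at r = 0.8, 10.5% at r = 0.5 and 6.6% at r = 0.2.

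**4. Effect of non-return on preference.** Let p be the preference for the swab among returners, q the share of consenters who do not return it, and p0 the preference among those non-returners. Over all consenters, preference = p(1 − q) + p0 × q. All inputs are assumed. With p = 70%:

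- q = 10%: 0.63 + 0.10 × p0, which is 63% at p0 = 0 and 66% at p0 = 30%.
- q = 20%: 0.56 + 0.20 × p0, which is 56% at p0 = 0 and 62% at p0 = 30%.
- If p0 = p there is no bias.

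**The case against.** **Late pairs are permitted, not prescribed.** A reader might infer that the plan states that late swabs count in the 2x2 tables. It does not. The packs described under Trial process hold both a swab and a bulk container, so a re-sent pack could yield a fresh pair, and some participants will have returned neither sample. This stands, and the point is confined to what the rule allows.

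**Late pairs can be identified, and analysis sets belong in the SAP.** Collection times are recorded, so exclusion is feasible, and an article may leave analysis sets to a fuller document. This stands in part. The article does state a recovery rule, and that rule is not reconciled with the window in the Abstract. The extra testing of discordant pairs mentioned under Control sample and in the Discussion is not tied to the collection interval, so as described it does not deal with lateness.

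**The loss may be nil.** Chronic carriers are eligible, and with persistent shedding sensitivity does not move. This stands.

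**Comparison with the stopping margin.** A reader might set the loss in sensitivity against the final margin of 0.10 under Interim analysis. The documents do not support this, because Decision rules expresses its cutoff as a difference in accuracy. If accuracy means overall agreement, a 4.75-point loss in sensitivity at 30% positive is only 0.30 × 4.75 = 1.4 points.

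**Acceptability.** Asking people who tried both methods is a legitimate measure of comparative preference, and omitting withdrawn participants' data respects their consent. A reader might infer that every non-return is a rejection of the swab. The documents do not support that: recovery, lost post or failed contact are equally possible, and the Introduction notes reluctance about faecal samples too. What remains is that recording withdrawal reasons supplies no denominator and cannot cover people who were never reached.

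**Conclusion.** The point holds as a design weakness with two separate parts.

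First, the recovery rule conflicts with the 24-hour window, because it lets a replacement swab be paired with an earlier bulk sample without limit. If those pairs are analysed and shedding has fallen, sensitivity is biased downwards. With 10% of positive pairs late and 50-80% of those patients still shedding, 95% becomes 90-93%; with persistent shedding there is no loss. The direction depends on shedding, and the size rests on assumed inputs. The fair benchmark is the roughly 5-point precision implied by the 73 positives per subgroup, which 10.5% late pairs would use up if half still shed.

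Second, the preference outcome describes people who returned samples. It overstates acceptance among all consenters if non-returners like the swab less. By how much cannot be known without the non-return rate and the reasons for it.

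**What to change.** - **Methods:** state the 24-hour limit in Collection process, so that it does not rest on the Abstract alone.
- **Missing data:** either require that a replacement kit yields a new swab and a new bulk sample within 24 hours of each other, or keep out-of-window pairs out of the primary 2x2 tables and use them only in a sensitivity analysis by interval.
- **Acceptability:** report swab-return and bulk-return proportions and the recorded reasons for non-return among all consenters, as far as consent allows, alongside preference among those who completed both samples. Ask about preference or reason at the check-in contact already planned for unreturned swabs.
- **Non-return as rejection:** use this only as a labelled worst-case sensitivity analysis.

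**Cost:** a few pairs lost from the primary tables, or one repeat bulk test for each, plus a short change of wording. Collection times are already minimum data and the check-in contact already exists. Preferences not asked at that contact would be hard to recover later.
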